**Asymptomatic bacteriuria of ≥10^5^ cfu/ml treated with antibiotics**

This outcome will be assessed based on the information from the previous listed outcomes. Events will be counted if patient received antibiotics based on a bacteriuria ≥10^5^ cfu/ml without any symptomatic signs for a UTI.

**Detection of multidrug-resistant bacteria in urine culture**

Routine urine culture and resistance patterns are performed prior to the surgery, at day 3 and day 30. Urine culture are found in the hospital information system.

1. Before the patient arrives the clinician who will perform the routine control or the study nurse will consult the hospital information system and assess the urine culture result and the resistance pattern.
2. Depending on these results 3MRGN and 4MRGN is assessed according to the definition by the Robert Koch Institute (34).
3. If a patient reported during the assessment that another physician was consulted (see section “9.2.1 Assessment of primary outcome”) the clinician will contact the corresponding to receive the corresponding urine culture results with resistance pattern. Resistance pattern and 3MRGN and 4MRFN will be assessed as described in 1) and 2).

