# STUDY OUTCOMES

All outcomes are events within 30 days (±5 days) after randomisation if not otherwise stated.

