### 9.2.2 Assessment of secondary outcomes

**Symptomatic UTI (based on clinical diagnosis supported by measured bacteriuria of ≥10^5^ cfu/ml) treated with antimicrobial agents (key secondary outcome)**

The key secondary outcome will be assessed in the same way as the primary outcome (see section “9.2.1 Assessment of primary outcome”) within the same procedure and from the same persons to be contacted. Whenever the primary outcome occurred, it will be assessed in the hospital system and in the contacting of the physicians, if this event was confirmed by a bacteriuria of ≥10^5^ cfu/ml. Urine cultures are performed at day 3 and day 30 as well during unscheduled visits. Urine culture results can be found in the hospital information system. From all urine samples it will be recorded in the eCRF how they were collected (i.e. midstream, from catheter). We will consider possible between-group differences in this regard in the interpretation of this outcome.

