### 9.3.6 Follow-up after 30 days

All endpoints will be assessed at day 30 (±5 days; for more details see Section 9.2.1-9.2.4). In case that a patient will not conduct the 30 day visit, the treating physician or the study nurse will try to find an alternative date within the 5 day window. If this is not possible, the requested information for the primary endpoint will be asked by phone.

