### 11.4.3 Secondary Analyses

Secondary analyses will be exploratory in nature and aim to measure the ITT effect. All estimates will be presented with 95% confidence intervals.

The key secondary outcome a (Symptomatic UTI (based on clinical diagnosis supported by measured bacteriuria of ≥10^5^ cfu/ml) treated with antibiotics*)* will be analysed as described for the primary endpoint (Section 11.4.2). Results (size and direction of the effect) will be compared informally to the primary endpoint.

Secondary outcomes *b – m* (see Section 5.2) will be analysed with *generalised linear mixed models (GLMM) with binomial error distribution*, including trial arm as predictor and study centre as random effect. Estimates will be reported as odds ratios (OR).

Secondary outcomes *n – p* (see Section 5.2) will be treated as count data and analysed with *GLMM with poisson error distribution*, including trial arm as predictor and study centre as random effect. Estimates will be reported as relative effects.

Secondary outcomes *r – s* (see Section 5.2) will be analysed by means of linear mixed models (LMM), including trial arm as predictor and study centre as random effect. Estimates will be reported as absolute effects.

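### Detection of multidrug-resistant bacteria pools scheduled with event-driven urine cultures, so a difference between arms may partly reflect how often men were cultured; the effect is small and the remedy cheap.

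*Protocol*

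**What the plan says.** Detection of multidrug-resistant bacteria in urine culture is the tenth secondary outcome in section 5.2 (outcome j in the lettering of 11.4.3). The introduction to the outcomes section sets the window: "All outcomes are events within 30 days (±5 days) after randomisation if not otherwise stated".

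Three sources of cultures feed it:

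- **Scheduled cultures.** Section 9.2.2: "Routine urine culture and resistance patterns are performed prior to the surgery, at day 3 and day 30". Two of these come after randomisation.
- **Unscheduled visits.** The schedule in 9.1 marks this outcome at day 3, at unscheduled visits and at day 30. Under the key secondary outcome, 9.2.2 adds: "Urine cultures are performed at day 3 and day 30 as well during unscheduled visits".
- **Outside physicians.** Step 3 of the same part of 9.2.2 begins "If a patient reported during the assessment that another physician was consulted". The results are then requested and classified by the same rule as the scheduled ones.

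For a man who misses the day-30 visit and cannot be rescheduled, 9.3.6 says "the requested information for the primary endpoint will be asked by phone"; it provides for no culture.

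Section 11.4.3 assigns outcomes b to m to "generalised linear mixed models (GLMM) with binomial error distribution", "including trial arm as predictor and study centre as random effect", reported as odds ratios. Secondary analyses are described there as exploratory. Section 11.5 makes them primarily complete case, accepts that numbers will vary between analyses, and allows imputation or weighting when missingness is considerable.

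**The concern.** A resistant isolate can be found only if urine is cultured. Every man is due the same two post-randomisation cultures, but the further ones follow from events. Step 3 of the resistance assessment refers back to 9.2.1, where an outside physician is contacted when the patient reports an antibiotic or a UTI diagnosis, or when the primary endpoint is uncertain. The extra sampling is therefore tied to the primary outcome, which treatment may change. The model has no term for the number or type of cultures, and nothing in 9.2.2 or 11.4.3 separates scheduled from event-driven detections.

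The likely direction matters for interpretation. Section 11.2 accepts about 4 more UTIs per 100 men partly because single-dose prophylaxis should lead to fewer resistant pathogens. If the single-dose arm does have more UTIs, the resistance measure set against them is itself pushed upward by the extra culturing. The protocol shows awareness of a related issue for the key secondary outcome: it records how each urine sample was collected and will consider differences between arms. It says nothing comparable for resistance.

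**Working it through.** **Inputs from the protocol.** UTI rate 9% in both arms, margin 4.4 points and 1,416 evaluable men (11.2), hence 1,416 / 2 = 708 per arm. Two scheduled post-randomisation cultures per man (9.2.2). The protocol gives no figure for this outcome. The sample size used for scale does reproduce: the continuity-corrected Wilson-based interval gives 80.2% power at 1,416, and 1,416 / 0.9 rounds up to 1,574.

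**Assumptions.** UTI 13.4% (9% + 4.4%) in the single-dose arm against 9%; one extra culture per UTI; equal underlying resistance. All resistance rates below are assumed.

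**Step 1: how unequal is the testing?** Extra cultures per 708 men: 708 × 0.09 = 63.7 and 708 × 0.134 = 94.9. Cultures per man: 2.090 against 2.134, and 2.134 / 2.090 = 1.021, so 2.1% more.

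**Step 2: the extra culture only re-samples stable carriage.** Let c be carriage (1% to 5%), s the sensitivity of one culture (0.5 to 0.9), a the share of scheduled cultures done (70% to 100%) and u the UTI rate. Then

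detection = c × [(1 − u) × (1 − (1 − as)²) + u × (1 − (1 − as)² × (1 − s))].

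At c = 5%, s = 0.5, a = 0.7 this gives 3.029% against 2.983%: a difference of 0.046 points and an odds ratio of 1.016. Over the whole grid the odds ratio runs from 1.000 to 1.016.

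**Step 3: the extra culture can reveal an isolate not otherwise found.** Let b be detection from scheduled cultures and q the probability that the extra culture shows a resistant isolate missed by them. Then

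detection = 1 − (1 − b)(1 − uq).

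| b | q | 13.4% UTI arm | 9% UTI arm | Odds ratio | Extra positives per 708 |
|---|---|---|---|---|---|
| 1% | 3% | 1.40% | 1.27% | 1.10 | 0.9 |
| 1% | 5% | 1.66% | 1.45% | 1.15 | 1.5 |
| 1% | 10% | 2.33% | 1.89% | 1.24 | 3.1 |
| 2% | 3% | 2.39% | 2.26% | 1.06 | 0.9 |
| 2% | 5% | 2.66% | 2.44% | 1.09 | 1.5 |
| 2% | 10% | 3.31% | 2.88% | 1.15 | 3.1 |
| 3% | 3% | 3.39% | 3.26% | 1.04 | 0.9 |
| 3% | 5% | 3.65% | 3.44% | 1.06 | 1.5 |
| 3% | 10% | 4.30% | 3.87% | 1.12 | 3.0 |

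**Step 4: sensitivity of the largest cell (b = 1%, q = 10%).**

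- UTI 10% against 9%: odds ratio 1.05.
- Only half of UTIs yield an extra culture (u = 6.7% against 4.5%): odds ratio 1.15.
- Equal UTI rates: odds ratio 1.
- Sampling error: 16.5 against 13.4 positives per 708 men gives an approximate 95% interval of 0.60 to 2.56 around 1.24.

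**Step 5: who is evaluable?** Setting 9.3.6 beside 11.5, a man with a negative day-3 culture and telephone follow-up could be coded negative (one result available) or missing (day-30 culture absent). Section 11.5 tells the analyst to use complete cases but does not say which cultures make a case complete. Its trigger for imputation or weighting, more than 5% missing in one group, cannot be applied until that is settled.

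**The case against.** The strongest case against runs as follows.

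- **The schedule is common to both arms.** Two planned cultures per man dominate the testing, and the extra ones shift the total by about 2% even at the full margin. This stands, and it is why the effect is small.
- **The illustration is close to a worst case.** Planning assumes equal UTI rates. The primary outcome is a clinical diagnosis that needs no culture, and UTIs found in hospital or at the day-30 control may coincide with scheduled cultures. One extra culture per UTI is nearer an upper bound, and q has no source in the protocol. This stands too.
- **Part of any excess is real.** If single-dose prophylaxis leads to more UTIs and some grow resistant bacteria, those infections are a consequence of the strategy. That is a sound reason to keep the any-culture outcome. It does not help a reader separate more resistance from more testing.
- **Restricting to scheduled cultures has its own bias.** It drops resistant isolates from infections between visits, the day-30 culture may be altered by antibiotics given for an earlier UTI, and attendance is itself post-randomisation. This argues against replacing the outcome, and especially against a day-30-only definition. It does not argue against a second comparison alongside.

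A reader might also infer that the outcome is taken over all randomised men and that a man without a culture counts as free of resistant bacteria. The documents do not support this. Section 9.2.2 classifies men from culture results, and 11.5 points to complete cases with varying numbers. What is missing is the definition of an evaluable man, not a rule that codes absence as negative.

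**Conclusion.** The point holds in a limited form. Scheduled and event-driven cultures are pooled into one any-positive result, and the specified analysis ignores how often each man was cultured. A difference between arms could therefore reflect testing in part, but only if UTI or consultation rates differ.

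With UTI at 13.4% against 9%, equal underlying resistance and one extra culture per UTI, the spurious odds ratio lies between about 1.00 and 1.24 over the assumed ranges, at most about 3 extra positives per 708 men. That is well within sampling error for this outcome. It would be wrong to read the point as showing that the resistance comparison is seriously biased or that the single-dose arm will be tested more.

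The outcome is one of 19 secondary outcomes, all exploratory, and the non-inferiority conclusion does not depend on it. Because resistance is central to the trial's rationale, clarification is still worth making.

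**What to change.** In 9.2.2 and 11.4.3:

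1. Keep detection in any culture within 30 days as the outcome.
2. Add a pre-specified comparison restricted to the scheduled day-3 and day-30 cultures, among men with a result, with no culture treated as missing. State how a man with only one of the two results is handled.
3. Report by arm the number of men cultured, the number of cultures per man, and, separately, detections that came only from unscheduled or outside cultures.

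The cost is wording and one more exploratory analysis; the cultures are already in the plan. The added comparison will have fewer detections and a wider interval, and its day-30 component may be affected by antibiotics given for an earlier UTI, so it should be read beside the any-culture outcome and not instead of it.

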**Any *Clostridium difficile*-associated infection**

The following procedure will be performed at day 30. First, before the patient arrives the clinician who will perform the routine control or the study nurse will consult the hospital information system and assess if the endpoint occurred during the hospital stay or if the patient was re-hospitalized due to a ‘*Clostridium difficile*-associated infection’, documented by microbiological method according to guidelines issued by the European Society for clinical microbiology & infection (ESCMID) (35). During the routine control, the clinician will check if the patient has symptoms and/or signs suggestive of a *Clostridium difficile*-associated infection. If yes, specific microbiological stool tests are performed (depending on the respective local algorithm at each study center for diagnosing a *Clostridium difficile*-associated infection).

**Duration of catheterisation (cumulative sum of catheter days between randomisation and day 30)**

At the routine control the study nurse will enter the day of catheter removal into the eCRF based on the information provided in the hospital information system. Additionally, it will be reported if subsequent catheters were used (including the date of application and removal). Based on these data the duration of catheterisation will be calculated.

**Duration of hospital stay (cumulative sum of hospital days between randomisation and day 30)**

At day 30 the study nurse will enter the discharge day after randomisation into the eCRF by consulting the hospital information system. Furthermore, the hospital information system will be consulted and the patient is asked, if between hospital discharge and routine control hospitalisation (days) occurred. In case that the patient reports that the endpoint occurred between hospital discharge and routine control (i.e. another hospital; and also if any uncertainty about the non-occurrence of the endpoint exists) the clinician will contact the corresponding physician and gets the information. The days of re-hospitalisations and the days of discharges will be reported. Based on these information the duration of hospital stay will be calculated.

**Duration of intensive care unit stay (cumulative sum of ICU days between randomisation and day 30)**

At the routine control, the study nurse calculates the total days of ICU stay by consulting the hospital information system. Furthermore, the patient is asked, if between hospital discharge and routine control, a rehospitalisation and ICU stay has occurred and for how long (days). In case that the patient reports that a rehospitalisation/ICU stay occurred between hospital discharge and routine control (i.e. at another hospital; and also if any uncertainty exists), the clinician will contact the corresponding physician and will obtain the respective information.

**Re-Hospitalisation (within 30 days after randomisation)**

See endpoint ‘Duration of hospital stay”.

**Change of International Prostate Symptom Score (prior to randomisation and at day 30 after randomisation)**

Prior to the surgery and at the routine control at day 30, patients are routinely handed out the validated International Prostate Symptom Score (36) consisting of 7 questions. Each question concerning urinary symptoms allows the patient to choose one out of six answers indicating increasing severity of the particular symptom. The answers are assigned points from 0 to 5. The total score can therefore range from 0 to 35 (asymptomatic to very symptomatic). The change of the score is calculated by subtracting the score at day 30 from the score at enrolment.

**Change of Quality of life Score (prior to randomisation and at day 30 after randomisation)**

Prior to the surgery and at the routine control at day 30, patients are routinely handed out the International Prostate Symptom Score (36, 37). This questionnaire is added by the Quality of life Score (36) consisting of one question allowing the patients to choose one out of seven answers from 0-6 (delighted – terrible). The change of the score is calculated by subtracting the score at day 30 from the score at enrolment.

**All-cause mortality**

First, before the patient arrives the clinician who will perform the routine control or the study nurse will consult the hospital information system and assess if the endpoint occurred during the hospital stay or if the patient was re-hospitalised and the endpoint occurred. In case the patient misses the follow-up routine control at 30 days, the study nurse consults the patient by phone. If the patient is not available, the treating physician (e.g. general practitioner) is called to assess the endpoint and, if applicable, the date and cause of mortality.

### 9.2.3 Assessment of other outcomes of interest

There are no further outcomes planned to be assessed.

### Assessment of safety outcomes

#### 9.2.4.1 (Serious) Adverse events

To assess any potential harms, the study team evaluates SAE according to the ICH E2A guidelines (38) as “definitely”, “probably”, “possibly”, “unlikely” and “not related”. The “Common Terminology Criteria for Adverse Events”, Version 5.0 terminology is going to be used for (S)AE occurring throughout this study: 1 – Mild (does not influence activities of daily living), 2 – Moderate (influences activities of daily living), 3 – Severe (makes some activities of daily living impossible), 4 – Life-threatening, 5 – Death. For further information please refer to Section 10.1.1. The study personnel will automatically be reminded at any study visit (planned or unplanned) from the time point of final treatment allocation to assess SAE on a separate form if any occurred. At day 3, AEs of special interests (e.g. diarrhea, nausea, vomiting, allergic reaction, and neurological disorder) will be assessed. Additionally, other not pre-specified AEs can be entered into the eCRF.

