| Outcome(s): | All outcomes are events within 30 days (±5 days) after randomisation if not stated otherwise. Primary outcome measure Symptomatic UTI (based on clinical diagnosis) treated with antimicrobial agents. Secondary outcome measuresSymptomatic UTI (based on clinical diagnosis supported by measured bacteriuria of ≥10^5^ cfu/ml) treated with antimicrobial agents (**key secondary outcome**)  - Symptomatic cystitis (based on clinical diagnosis) - Symptomatic epididymitis (based on clinical diagnosis) - Symptomatic pyelonephritis (based on clinical diagnosis) - Symptomatic prostatitis (based on clinical diagnosis) - Symptomatic urethritis (based on clinical diagnosis) - Urosepsis (based on clinical diagnosis) - Prescription of antibiotics (for any reason) - Prescribed defined daily doses (DDD) of antibiotics (cumulative sum of DDD from randomisation to day 30) - Asymptomatic bacteriuria of ≥10^5^ cfu/ml treated with antimicrobial agents - Detection of multidrug-resistant bacteria in urine culture (3MRGN, 4MRGN) - Any *Clostridium difficile*-associated infection - Duration of catheterisation (cumulative sum of days between randomisation and end of catheterisation or day 30) - Duration of hospital stay (cumulative sum of hospital days between randomisation and day 30) - Duration of intensive care unit stay (cumulative sum of ICU days between randomisation and day 30) - Re-hospitalisation (within 30 days after randomisation) - Change of International Prostate Symptom Score (prior to randomisation and at day 30 after randomisation) - Change of Quality of life Score (prior to randomisation and at day 30 after randomisation) - All-cause mortality - Total adverse events - Total serious adverse events |
| Study design: | Pragmatic, placebo controlled, parallel arm, non-inferiority, multicentre, randomised controlled trial based on routinely collected data with blinded treating physicians, patients and outcome assessors. |

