| 1. Duration of catheterisation (cumulative sum of days between randomisation and end of catheterisation or day 30) |  |  |  |  |  | X |
| 1. Duration of hospital stay (cumulative sum of days between randomisation and discharge or day 30) |  |  |  |  |  | X |
| 1. Duration of intensive care unit stay (cumulative sum of days between randomisation and discharge from ICU or day 30) |  |  |  |  |  | X |
| 1. Prescribed defined daily doses (DDD) of antibiotics (cumulative sum of DDD from randomisation to day 30) |  |  |  |  |  | X |
| 1. Change of International Prostate Symptom Score (prior to randomisation and at day 30 after randomisation) | X |  |  |  |  | X |
| 1. Change of Quality of life Score (prior to randomisation and at day 30 after randomisation) | X |  |  |  |  | X |
| Adverse events |  |  |  | X |  |  |
| Serious adverse events |  | X | X | X | X | X |
| Concomitant care | X |  |  | X |  | X |

Abbreviations: AP, antimicrobial prophylaxis; ASA, American Society of Anesthesiologists; BMI, body mass index; cfu, colony-forming units; DDD, defined daily doses; ID, identification (number); ICU, intensive care unit; PSA, prostate specific antigen; UTI, urinary tract infection.

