### 10.1.3 Follow-up of (Serious) Adverse Events

During the study every step is taken to ensure, that all (S)AEs are identified and documented. Treating doctors and study centers are responsible to treat the (S)AEs and follow-up (S)AEs. At the routine follow-up at day 30 it is ensured, that all (S)AEs are identified and well treated. If a (S)AE occurs, all efforts will be undertaken to treat these (S)AEs (e.g. antiallergic treatment in case of an allergic reaction) and follow-up until it is resolved is ensured.

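### The protocol contradicts itself on the adverse event window: total AEs is a 30-day outcome, but non-serious AEs are scheduled for assessment on day 3 only

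*Protocol*

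**What the plan says.** **Thirty days.** The synopsis sets a default for every outcome: "All outcomes are events within 30 days (±5 days) after randomisation if not stated otherwise". Its list ends with "All-cause mortality - Total adverse events - Total serious adverse events" and gives no other window for these items. Section 5 repeats the default ("All outcomes are events within 30 days (±5 days) after randomisation if not otherwise stated") and names AEs and SAEs as the safety outcomes. Section 9.3.6 says that all endpoints are assessed at day 30 and refers to sections 9.2.1 to 9.2.4, which include the safety section. Section 10.1.3 says: "At the routine follow-up at day 30 it is ensured, that all (S)AEs are identified and well treated".

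**Day 3.** The columns of the table in section 9.1 are enrolment, day 0, days 1 and 2, day 3, unscheduled visits and day 30. The AE row has a single mark, at day 3: "Adverse events | | | | X". The row below it is marked from day 0 to day 30: "Serious adverse events | | X | X | X | X | X". Section 9.2.4.1 gives the time point in words: "At day 3, AEs of special interests (e.g. diarrhea, nausea, vomiting, allergic reaction, and neurological disorder) will be assessed". It adds that other AEs can be entered in the eCRF, without saying when. The automatic reminder at each visit described there concerns SAEs. Section 9.3.4 puts both the AEs of special interest and other potential AEs at day 3. Section 10.1 commits to collecting SAEs for the whole study and makes no such commitment for non-serious AEs.

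**The concern.** An outcome defined over 30 days needs a procedure that observes 30 days. For non-serious AEs the schedule provides one assessment, on the day after the last tablet. A site that works from the table and section 9.2.4.1 would stop asking at day 3. A site that works from section 10.1.3 would ask again at day 30. Both would be following the protocol.

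The AE comparison is part of the case for the trial. Section 11.2 supports the acceptability of the 4.4-point margin partly by expecting fewer individual adverse events with the single dose, and the section on risks and benefits expects the same. A blinded, placebo-controlled trial can test that expectation, provided that the AE count has one stated window that all sites apply.

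**Working it through.** The plan gives no AE rate, so it has no AE figure to reproduce. The sample size (1,416 evaluable, 1,574 recruited) does not use AE data. The check sets the statements side by side and then asks what follows.

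**1. The statements**

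| Place in the protocol | Window or time point for non-serious AEs |
| --- | --- |
| Synopsis, outcomes | 30 days (±5), by default |
| Section 5, opening sentence and safety outcomes | 30 days (±5), by default |
| Section 9.3.6 | day 30, through the reference to 9.2.4 |
| Section 10.1.3 | day 30 |
| Section 9.1, AE row | day 3 only |
| Section 9.2.4.1 | day 3 for the special-interest list; other AEs may be entered, no time given |
| Section 9.3.4 | day 3 |
| Section 9.2.4.1, visit reminder | SAEs only |
| Section 10.1 | SAEs only |

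The reference in 9.3.6 does not settle the matter: it points to 9.2.4 for detail, and 9.2.4.1 gives day 3.

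**2. The part of the window with a scheduled check**

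- Dosing: one tablet on the evening of day 0 and two on each of days 1 and 2, the last after dinner on day 2 (sections 8.2.1 and 9.3.2). The AE check is on day 3.
- Days covered: 3/30 = 10%. Over the ±5-day tolerance: 3/35 = 8.6% to 3/25 = 12%.
- Days without a scheduled AE assessment: 30 − 3 = 27, or 90%.

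These are shares of calendar days. They are not shares of events, which need not be spread evenly over the month.

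**3. What could happen to the comparison between arms**

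The protocol gives neither AE risks nor onset times. As an assumption for illustration only, take 30-day AE risks of 10% (3-day arm) and 5% (single dose), a true difference of 5 points. Let s be the share of events that start after day 3 and go unrecorded.

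| s | Same share in both arms: (10 − 5)(1 − s) | Late events in the 3-day arm only: 10(1 − s) − 5 | Late events in the single-dose arm only: 10 − 5(1 − s) |
| --- | --- | --- | --- |
| 0 | 5 | 5 | 5 |
| 0.10 | 4.5 | 4.0 | 5.5 |
| 0.25 | 3.75 | 2.5 | 6.25 |
| 0.50 | 2.5 | 0 | 7.5 |

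With an equal late share the risk ratio stays at 10/5 = 2, because (1 − s) cancels. With no late onset nothing changes. The difference can therefore shrink, grow or stay the same, and the document does not say which case applies.

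**4. Mixed practice between sites**

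Centre is a minimisation factor (section 6.2.1), so sites with a short and a long window should contribute to both arms in similar proportion, and the assessors are blinded. Mixed practice would thus mainly leave the pooled count without a defined window, rather than favour one arm.

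**The case against.** The strongest reply is that the protocol does provide for AEs after day 3. Section 10.1.3 promises that all (S)AEs are identified and documented, including at day 30. Section 9.2.4.1 allows other AEs to be entered without a time limit. At day 30 patients are asked about symptoms since discharge and whether a physician was consulted (section 9.2). SAEs, *C. difficile* infection, re-hospitalisation, death and antibiotic prescriptions with their reason are all followed to day 30. The AE analysis is descriptive, without tests (section 11.4.5).

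Much of this stands. A reader might infer that AEs are collected only once, that later drug reactions are missed, or that late events are lost altogether. The text does not support that: it promises day-30 identification in one place and schedules day 3 in another, and serious late reactions are covered.

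The reply does not remove the contradiction. Section 10.1.3 names no form, no question list and no mark in the schedule. The day-30 symptom question is aimed at UTI and antibiotic use and is not tied to AE recording. When the visit is missed, section 9.3.6 limits the telephone call to the primary endpoint. Free entry of other AEs is optional. Section 10.1.1 does not count prolonged hospitalisation as an SAE, so a late event whose only consequence is a longer stay may fall outside both routes.

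**Conclusion.** The point holds as an internal contradiction. Total AEs has a 30-day window by definition and a day-3 assessment by schedule. Non-serious AEs that start after day 3 have no scheduled collection point, sites may apply different windows, and the 30-day AE count by arm would be incomplete.

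A reader might go further and conclude that the harm of the longer course is understated. That is possible, but the document does not show it. It would need AE rates and onset times that the protocol does not give, and under other equally unsupported assumptions the observed difference would be unchanged or larger. If under-counting did fall mainly on the 3-day arm, it would weaken the expected advantage of the single dose rather than help it.

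The consequence is confined to a descriptive safety table. The margin is calculated from the 9% rate, the risk ratio of 0.38 and 70% preservation; fewer AEs is a supporting remark in section 11.2 and not an input. The primary non-inferiority analysis and the sample size are unaffected. The point should be corrected because it is cheap to correct and decides what the AE comparison can show.

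**What to change.** Choose one window and state it everywhere.

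- **Keep 30 days.** Mark AEs at unscheduled visits and at day 30 in the table in section 9.1. Ask the same AE-of-special-interest list at the existing day-30 visit, covering the time since day 3, and add it to the telephone call in section 9.3.6 for patients who miss the visit. Amend 9.2.4.1 to match. The cost is one more short eCRF form at a contact that already takes place, and a small amendment.
- **Or limit the outcome to day 3.** Define total AEs as events from randomisation to day 3 and correct the synopsis, section 5, 9.3.6 and 10.1.3. This needs no new data collection, but the trial could then say nothing systematic about non-serious AEs that start later.

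The first option fits the outcome as now defined and the benefit claimed in section 11.2. If patients have already been followed under the present text, the report should state which window each site used.
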